## Abstract

**Background:**

Gastrointestinal adverse events (GI AEs) are the main dose-limiting side effects of metformin in type 2 diabetes mellitus (T2DM), reducing adherence and compromising long-term glycaemic control. Current strategies (dose adjustment or combination therapy) seldom address both tolerability and sustained metabolic efficacy. Transcutaneous auricular vagus nerve stimulation (taVNS) is a non-invasive neuromodulation technique that may modulate gut–brain–metabolic pathways—vagal reflexes, inflammation, intestinal barrier function, and enteroendocrine signaling—and thus improve drug tolerance while preserving glycaemic control.

**Methods:**

This single-center, randomized, sham-controlled pilot trial will enroll 60 T2DM patients with metformin-associated GI AEs, randomized 1:1 to either the taVNS group or the sham control group. The intervention lasts 2 weeks with a follow-up at week 4. Assessments at baseline and follow-up include a validated Metformin Symptom Severity Score (total score 0–50; primary outcome), Bristol Stool Form Scale, bowel urgency, glycaemic/metabolic indices [fasting blood glucose (FBG), 2-h postprandial glucose (PG2h), glycated albumin (GA), fasting C-peptide, fasting insulin, HOMA-IR, ISI], and mechanistic biomarkers (GLP-1, 5-HT, IL-6, IL-10, TNF-α, D-lactate, DAO, bile acids). Safety monitoring includes routine hematology, liver and renal function tests.

**Discussion:**

By combining clinical outcomes with targeted biomarker analyses in a randomized design, this pilot study will assess whether taVNS alleviates metformin-associated GI intolerance without impairing glycaemic efficacy, and will provide feasibility data, effect-size estimates, and biomarker selection for future confirmatory trials.

**Clinical trial registration:**

Trial registration International Traditional Medicine Clinical Trial Registry (ITMCTR) http://itmctr.ccebtcm.org.cn/, Identifier: ITMCTR2025001086.

## Introduction

1

Type 2 diabetes mellitus (T2DM), characterized by insulin resistance and impaired insulin secretion, is increasing in prevalence and constitutes a major global public-health challenge (Giaccari et al., 2012). Metformin is universally recommended as first-line therapy in contemporary diabetes guidelines because of its favorable safety profile, cost-effectiveness, and demonstrated long-term safety—a recommendation supported by several high-quality meta-analyses (Maruthur et al., 2016; Palmer et al., 2016). Emerging evidence further indicates that, beyond glycaemic control, metformin exerts pleiotropic effects including cardiovascular protection and antineoplastic actions (Rena et al., 2013; Rojas and Gomes, 2013).

However, gastrointestinal adverse events (GI AEs) are the most common dose-limiting side effect of metformin and substantially impair treatment adherence and long-term outcomes. Reported non-adherence to metformin reaches 43%, notably higher than rates observed for statins (36%) or angiotensin-converting enzyme inhibitors (23%) (Pladevall et al., 2004). In a randomized study of over 1,400 patients with T2DM, 23.7% of participants assigned to metformin experienced diarrhea, 15.4% reported abdominal discomfort, 11.7% reported nausea, and 5.8% experienced vomiting—rates higher than in the glibenclamide or rosiglitazone arms (Kahn et al., 2006). These adverse effects not only undermine adherence but also substantially diminish quality of life (Pladevall et al., 2004; Florez et al., 2010). Although dose reduction can improve tolerability, it concomitantly attenuates dose-dependent glycaemic efficacy (optimal effects are typically observed at doses approaching 2,000 mg/day), underscoring the clinical value of interventions that preserve both tolerability and efficacy (Garber et al., 1997).

Mechanistically, metformin-related GI AEs center on drug–gut interactions. Oral bioavailability of metformin is only ~50–60%, yet its antihyperglycaemic effects often exceed those of intravenous administration (Stepensky et al., 2002), and intestinal mucosal concentrations are markedly higher than plasma levels (Bailey et al., 1994; Mccreight et al., 2016)—all indicating that the gut is a principal site of action. Metformin stimulates L-cell secretion of glucagon-like peptide-1 (GLP-1) and may weakly inhibit dipeptidyl peptidase-4 (DPP-4), thereby increasing active GLP-1; elevated GLP-1 can delay gastric emptying and alter intestinal transit (Migoya et al., 2010). Structurally similar to certain 5-HT3 receptor agonists, metformin can promote enterochromaffin 5-hydroxytryptamine (5-HT) release and may impair 5-HT uptake by inhibiting organic cation transporters (OCT1, OCT3) and the serotonin transporter (SERT), leading to increased 5-HT availability and altered gut motility (Yee et al., 2015; Mawe and Hoffman, 2013). Metformin also perturbs bile acid handling by reducing intestinal bile salt hydrolase activity and increasing ileal bile flow, which can impair bile acid reabsorption and, through bile acid–microbiota interactions, further modulate GLP-1 secretion (Carter et al., 2003; Beysen et al., 2012). Additionally, the gut is a major site of lactate production; metformin raises intestinal lactate concentrations [confirmed in human jejunal biopsies (Mccreight et al., 2016)] and inhibits hepatic mitochondrial glycerol-3-phosphate dehydrogenase, reducing lactate clearance and promoting local accumulation that may directly irritate the mucosa (Bailey et al., 1992; Madiraju et al., 2014). Reduced OCT1 activity or genetic polymorphisms can increase intraluminal metformin accumulation, exacerbate anaerobic metabolism, and augment lactate generation (Singh et al., 2023; Dujic et al., 2016). Barrier dysfunction and ensuing inflammatory mediators, together with altered levels of GLP-1, 5-HT, IL-6, IL-10, TNF-α, D-lactate, diamine oxidase (DAO), and bile acids, contribute to dysbiosis—reported increases in taxa such as Akkermansia spp. and certain γ-Proteobacteria have been observed in T2DM patients (Shin et al., 2014)—and dysbiosis may in turn promote symptomatology by increasing pathogenic factor release and disrupting bile-acid metabolism (Ramos et al., 2016).

Because adherence is inversely associated with glycaemic control and directly associated with reduced healthcare costs (Lawerence et al., 2006), sustained metformin use is critical for disease management. Given the dose-dependent nature of metformin's efficacy [with optimal glycaemic effects observed near 2,000 mg/day (Garber et al., 1997)], attenuating GI AEs without reducing dose has important implications for treatment outcomes. Current clinical management largely relies on dose adjustment or adjunctive symptomatic therapies and lacks a systematic, mechanism-based “enhance-efficacy/reduce-toxicity” strategy rooted in the gut–brain–metabolic axis.

Against this pathophysiological background, non-invasive vagal modulation via transcutaneous auricular vagus nerve stimulation (taVNS) offers a novel therapeutic perspective. taVNS selectively activates the auricular branch of the vagus nerve (ABVN) and, through an ear–vagus–brainstem–gut circuit (Zou et al., 2026), can modulate central-peripheral autonomic balance, engage cholinergic anti-inflammatory pathways, regulate gut motility, influence endocrine mediators (including GLP-1 and 5-HT), and affect bile-acid metabolism, while indirectly reshaping the gut microbiota and barrier function (The Wingate Institute of Neurogastroenterology TBI, 2020; Seitz et al., 2022; Zhao et al., 2025; Zhang et al., 2025; Zou et al., 2024). Thus, taVNS could theoretically mitigate local inflammation and functional perturbations induced by metformin without necessitating dose reduction, thereby improving tolerability and synergistically enhancing metabolic control. The ear concha region corresponds anatomically to a dense distribution of ABVN fibers (The Wingate Institute of Neurogastroenterology TBI, 2020); transcutaneous stimulation of this area activates vagal pathways while avoiding the invasiveness of implanted VNS and can influence both gastrointestinal function and glucose metabolism (Zou et al., 2024; He et al., 2013).

Given the multifactorial mechanisms underlying metformin-induced GI AEs, taVNS may exert therapeutic effects through multiple converging pathways: modulation of the gut microbiota (e.g., reduction of certain opportunistic taxa) and bile-acid metabolism (Zhang et al., 2025); down-regulation of proinflammatory cytokines such as TNF-α and IL-6 via vagal-cholinergic anti-inflammatory signaling (Zhao et al., 2025); bidirectional regulation of 5-HT and GLP-1 to counteract metformin-induced elevations (Yang et al., 2026); and reduction of serum D-lactate levels with consequent improvement of mucosal barrier function (Seitz et al., 2022). Importantly, taVNS may also enhance vagal efferent activity and physiologic GLP-1 secretion, thereby complementing metformin's insulin-sensitizing actions and supporting improved glycaemic management (Yee et al., 2015).

It should be emphasized that traditional ear-acupoint localization (for example, spleen and colon regions in auricular acupuncture) provides historical and anatomical rationale for stimulation site selection, but mechanistic validation requires imaging, electrophysiological, and molecular evidence. Overall, taVNS presents a testable mechanistic hypothesis to resolve the “enhance-efficacy/reduce-toxicity” dilemma of metformin and merits systematic evaluation in randomized clinical and translational studies.

## Methods

2

### Study design

2.1

This study is designed as a single-center, randomized, sham-controlled clinical trial conducted at Wangjing Hospital, China Academy of Chinese Medical Sciences. The trial aims to evaluate the efficacy of taVNS in alleviating metformin-associated GI AEs and to explore its underlying mechanisms in improving drug tolerance and synergistically enhancing glycaemic control through analyses of molecular, metabolic, and inflammatory biomarkers.

The trial is designed in accordance with the Standard Protocol Items: Recommendations for Interventional Trials (SPIRIT) guidelines. Participant recruitment is expected to commence in December 2025, with completion of primary follow-up anticipated by March 2026. Eligible participants who meet all inclusion and exclusion criteria and provide written informed consent will be randomly assigned (1:1) to either the taVNS intervention group or the sham stimulation control group. The intervention period will last 2 weeks, followed by a 4-week post-treatment follow-up.

The protocol has been approved by the Institutional Ethics Committee (approval number: WIEC-YJS-2025-003-P002). To ensure participant safety and data integrity, an independent Data Monitoring Committee (DMC) has been established. The DMC will conduct periodic reviews of adverse events, trial conduct, and data quality.

A schematic flow of the study procedure is illustrated in Figure 1.

**Figure 1 F1:**
[figure not shown]
Schematic flow diagram of the study design.

### Recruitment

2.2

Participants will be recruited from the outpatient clinics of Wangjing Hospital, China Academy of Chinese Medical Sciences, via hospital posters, internal notices and the hospital's official WeChat account. The study team will screen potential participants against the predefined inclusion and exclusion criteria. Only individuals who meet all eligibility criteria and who provide written informed consent will be enrolled. All study data will be managed by authorized personnel; access will be restricted to designated, authorized members of the study team and the independent DMC. Personally identifiable information will be kept strictly confidential and stored in encrypted form in accordance with applicable institutional and national data-protection regulations.

### Diagnostic criteria

2.3

#### Diagnostic criteria for type 2 diabetes mellitus

2.3.1

The diagnosis of diabetes will follow World Health Organization (WHO) criteria (Puavilai et al., 1999; Kansagara et al., 2019). A diagnosis of T2DM will be made if any of the following criteria are satisfied:

(1) Fasting plasma glucose (FPG) ≥ 126 mg/dl (7.0 mmol/L) after an overnight fast of at least 8–14 h (venous or capillary);(2) 2-h postprandial venous plasma glucose ≥ 200 mg/dl (11.1 mmol/L);(3) 2-h postprandial capillary plasma glucose ≥ 220 mg/dl (12.2 mmol/L);(4) Random plasma glucose ≥ 200 mg/dl (11.1 mmol/L);(5) Glycated hemoglobin (HbA1c) ≥ 6.5%.

Borderline or inconclusive results should be repeated on a subsequent day. Typical hyperglycaemic symptoms (for example, polyuria, polydipsia, unexplained weight loss, or blurred vision) may support the diagnosis.

#### Diagnostic criteria for metformin intolerance

2.3.2

Metformin intolerance will be defined as meeting any of the following criteria (McCreight et al., 2018):

(1) Prior use of metformin with treatment discontinuation due to gastrointestinal intolerance (prior exposure ≤ 1,000 mg/day for ≤ 8 weeks); or(2) Inadequate glycaemic control [e.g., HbA1c ≥ 7.0% (53 mmol/mol)] with inability to escalate metformin to ≥500 mg/day because of intolerable gastrointestinal symptoms.

(Reference tolerability: individuals taking divided doses of metformin up to 2,000 mg/day without clinically significant gastrointestinal adverse effects.) Other causes of diarrhea must be excluded before confirming the diagnosis (McCreight et al., 2018).

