#### Inclusion criteria

2.3.3

Participants must meet all of the following:

(1) Fulfill the diagnostic criteria for T2DM and for metformin intolerance as defined above;(2) Aged 18–80 years (inclusive), any sex;(3) Able and willing to comply with study procedures and to provide written informed consent;(4) Stable diet, exercise, lifestyle and antihyperglycaemic regimen, with a fasting blood glucose coefficient of variation (CV) < 16% during the 3 days preceding baseline and on the day of enrollment;(5) Body mass index (BMI) between 18.5 and 40.0 kg/m^2^.

Only participants who satisfy all five criteria will be enrolled.

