#### Standard care (background therapy)

2.6.1

Background therapy follows international guideline recommendations and comprises standardized lifestyle counseling and medication management. Lifestyle counseling includes: dietary guidance with carbohydrates accounting for 45–60% of total daily energy intake and dietary fiber ≥25 g/day; at least 150 min/week of moderate-intensity aerobic activity (for example, brisk walking or cycling); and standardized education on disease management, medication adherence, and management of gastrointestinal symptoms to ensure consistency across participants (American Diabetes Association, 2024a,b).

Medication management principles are as follows:

Discontinue or avoid medications known to exacerbate gastrointestinal symptoms where clinically appropriate (e.g., stimulant laxatives or certain over-the-counter preparations);

In participants with inadequate glycaemic control, additional antihyperglycaemic agents (for example, SGLT2 inhibitors or DPP-4 inhibitors) may be added as clinically indicated, provided such additions are unlikely to aggravate gastrointestinal function; adjustments will follow current guideline recommendations and be documented;

Concomitant treatment for chronic conditions (e.g., antihypertensives for hypertension or secondary prevention therapies for coronary artery disease) will be maintained but clinicians should avoid introducing agents known to provoke GI intolerance when alternatives are available.

Metformin dosing will follow a “start low, escalate gradually” regimen: initial dose 500 mg administered with meals twice daily; dose titration will proceed weekly guided by fasting blood glucose (target 4.4–7.0 mmol/L), with a maximum dose up to 2,000 mg/day or the participant's maximal tolerated dose. Dose adjustments and all concomitant medications will be supervised and recorded by study physicians. In the event of severe, poorly tolerated diarrhea (e.g., ≥5 bowel motions per day with clinical signs of dehydration), metformin will be withheld or adjusted and symptomatic therapy provided (e.g., diosmectite); severe events will be managed according to the study Serious Adverse Event (SAE)—defined per the Common Terminology Criteria for Adverse Events (CTCAE) as any adverse event resulting in death, life-threatening illness, hospitalization, persistent disability, or requiring immediate emergency intervention—procedure and continue to be followed up (Rena et al., 2013).

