#### Primary efficacy outcome and assessment time points

2.7.2

The primary efficacy endpoint is the total score of the Metformin Symptom Severity Score, a validated, widely used self-report tool originally developed and psychometrically validated by McCreight et al. specifically for evaluating metformin-related gastrointestinal intolerance in adults with T2DM (McCreight et al., 2018).

In the original validation study by McCreight et al., this questionnaire demonstrated excellent reliability and validity: it showed strong internal consistency (Cronbach's α > 0.8), good test-retest reliability, and significant discriminant validity, with a highly significant difference in total scores between metformin-intolerant and metformin-tolerant patients (*P* < 0.0001) (McCreight et al., 2018). The questionnaire covers medication adherence, reasons for discontinuation, dose tolerance, gastrointestinal symptoms (nausea, abdominal bloating/pain, and diarrhea; frequency and subjective severity), changes in baseline symptoms, and an overall subjective tolerance rating, with a total score ranging from 0 to 50 points (0–10 = tolerable, 11–20 = mild intolerance, 21–30 = intolerable, 31–50 = severe intolerance). This questionnaire is used for the quantitative assessment of intolerance-related symptoms in this trial, not as a basis for clinical diagnosis.

Assessment time points include baseline, Week 2, and Week 4. Details of the questionnaire items and scoring criteria are provided in Table 2 (McCreight et al., 2018).

**Table 2 T2:** The metformin symptom severity score questionnaire.

No	Question	Option	Score
1	Are you still taking metformin?	Yes (skip to question 6)	0
		No	5
2	If you have stopped taking metformin, was it due to side effects?	Yes (continue to question 3)	5
		No (skip to question 6)	0
3	What dose were you taking at the time of discontinuing metformin?	500 mg once daily (1 tablet)	4
		1,000 mg once daily (2 tablets)	3
		500 mg twice daily (2 tablets)	2
		2,000 mg once daily (4 tablets)	1
		1,000 mg twice daily (2 tablets)	0
4	Have you ever taken a lower dose of metformin and tolerated it well?	Yes	0
		No	1
	If yes, what was the maximum dose you tolerated?	(e.g., 500 mg once daily)	2
5	Have you been trialed on a modified release preparation of metformin (e.g. Glucophage SR)?	Yes	2
		No	0
In the last week of taking metformin, have you experienced?			
6	Nausea?	Yes	1
		No	0
	If yes, how often?	More than once a day	4
		Once a day	3
		Occasionally	2

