#### Management of intervention- and drug-related AEs

2.8.2

Common adverse reactions related to taVNS include local pruritus, burning sensation, erythema/bruising, transient dizziness, or device displacement. Upon occurrence, stimulation should be immediately discontinued and participant status assessed; parameters may be adjusted or treatment terminated if necessary. Device malfunctions should be reported following the device adverse event protocol.

For metformin-related gastrointestinal intolerance (e.g., diarrhea, nausea, bloating), management should be guided by severity, including symptomatic support, dose adjustment, or switching to extended-release formulations. Severe dehydration, electrolyte imbalance, or life-threatening complications require immediate drug discontinuation and SAE management. All interventions (outpatient care, medication adjustments, hospitalization, referrals) must be documented and followed until resolution.

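### The intolerance criterion admits people who cannot reach 500 mg/day of metformin, yet everyone starts at 1,000 mg/day; later dose changes in continuing users are in no listed efficacy or feasibility outcome

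*Protocol article*

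**What the plan says.** **Eligibility.** Section 2.3.2 defines metformin intolerance by two alternative criteria, either of which is enough. Criterion (1) covers people who stopped metformin for GI intolerance after exposure of at most 1,000 mg/day. Criterion (2) covers people with inadequate glycaemic control "with inability to escalate metformin to ≥500 mg/day because of intolerable gastrointestinal symptoms". Section 2.3.3 makes this mandatory for entry: "Fulfill the diagnostic criteria for T2DM and for metformin intolerance as defined above".

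**Dosing.** Section 2.6 gives both arms metformin as background therapy. Section 2.6.1 describes a low start with gradual escalation: "initial dose 500 mg administered with meals twice daily", then weekly titration on fasting glucose "with a maximum dose up to 2,000 mg/day" or the participant's maximal tolerated dose. No other starting dose is given.

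**Later changes.** For severe diarrhoea, "metformin will be withheld or adjusted and symptomatic therapy provided" (2.6.1). For GI intolerance more generally, "management should be guided by severity, including symptomatic support, dose adjustment, or switching to extended-release formulations" (2.8.2). Sections 2.6.1 and 2.6.4 have dose and medication adjustments recorded and entered in the case report form.

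**Primary score.** In Table 2, item 1 asks whether the participant still takes metformin. The instruction beside the affirmative answer is "Yes (skip to question 6". Items 2 to 5, which include dose at stopping, tolerance of lower doses and modified-release use, are therefore not answered by continuing users.

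**The concern.** There are two linked problems.

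First, the eligibility threshold and the starting dose do not fit together. Someone admitted under criterion (2) is recorded as unable to reach 500 mg/day, and the protocol then starts that person at 1,000 mg/day. This is a matter of participant exposure. It also affects the data, since early intolerance in these participants would partly reflect the dosing rule.

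Second, the Introduction presents the value of the intervention as relief of GI symptoms without a cut in dose. Metformin dose can move up (for glucose) or down (for symptoms) after randomisation, and the weekly titration allows changes before the Week 2 assessment. If symptoms fall in one arm because more of its participants had their dose reduced or their formulation switched while continuing, the score improves and no listed efficacy or feasibility outcome gives the reason. Glycaemic results are affected by the same dose changes. A pilot meant to supply effect-size estimates and a standard deviation for a definitive trial needs dose by arm to interpret both sets of results.

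**Working it through.** **Step 1. Starting dose.** From 2.6.1: 500 mg × 2 per day = 1,000 mg/day.

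**Step 2. Comparison with criterion (2), including possible misprints.** The documents cannot show whether the 500 mg/day figure is intended, so the comparison is made over a range.

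| Reading of the threshold | Dose tolerated | Start ÷ tolerated |
|---|---|---|
| Cannot reach 500 mg/day (as written) | below 500 | 1,000 / (<500): more than 2 |
| Cannot exceed 500 mg/day | up to 500 | 1,000 / 500 = 2 or more |
| Cannot reach 1,000 mg/day | below 1,000 | more than 1; the start is the dose they cannot reach |
| Cannot reach a dose above 1,000 mg/day | may be 1,000 or more | no necessary conflict |

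Only a threshold above 1,000 mg/day removes the conflict.

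**Step 3. Do other provisions repair it?** The maximal-tolerated-dose wording in 2.6.1 is attached to the top of the titration, not to the first dose. The rules on withholding, adjusting or switching (2.6.1, 2.8.2) act after exposure and symptoms.

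**Step 4. What the primary score registers about dose.** From Table 2:

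- Stopped for side effects while on 500 mg twice daily: item 1 (No) 5 + item 2 (Yes) 5 + item 3 2 = 12. Over all item 3 options (0 to 4) the range is 10 to 14.
- Still taking metformin, at any dose or in any formulation: item 1 scores 0 and items 2–5 are skipped, so items 1–5 total 0.
- Maximum for a continuing user: 0 + 3 × (1 + 4 + 5) for the three symptoms + 3 for item 10 = 33. No part of this refers to current dose.

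Stopping is therefore scored. A participant cut to 500 mg/day and one raised to 2,000 mg/day, with the same symptoms and self-rating, score the same.

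**Step 5. Is dose listed elsewhere?**

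- Core feasibility endpoints (2.4): recruitment, screening failure, adherence to stimulation sessions, attrition and protocol violations. Dose is in 0 of 5. Dose changes made under the protocol's own rules would not count as violations.
- Secondary-outcome groups (2.7.3.1 to 2.7.3.5): 0 of 5.
- Table 1 outcome rows (1 primary + 9 secondary): 0 of 10.
- Statistical methods (2.10): only baseline metformin dose appears, as a covariate in the imputation model.

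**The case against.** **On the starting dose.** The maximal-tolerated-dose wording could be read as capping every dose, including the first. Re-exposing intolerant people is also part of the design, since criterion (1) admits people who stopped at up to 1,000 mg/day. Few people may qualify under criterion (2) as written, because the lowest dose in Table 2 is 500 mg once daily. Some of this stands: the number affected is unknown, and some re-exposure is intended. But the sentence gives an explicit initial dose and attaches the cap to the maximum. A cap on every dose would contradict that initial dose for these entrants, so the inconsistency remains.

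**On dose as an outcome.** The data are collected, exposure summaries are often left to an analysis plan, and a condensed article need not list every table. Adverse-event records must include interventions (2.8.1), and 2.9 compares events by arm, so a GI event that led to a dose action could appear there. This stands in part. A reader might infer that dose changes would be wholly invisible or go unreported; the documents do not support that. Adverse-event records are still only a partial substitute: they do not give dose over time, and titration on glucose need not produce an event.

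**On bias.** A reader might infer that the gap favours taVNS. The documents do not support a direction. Treating physicians have no access to allocation (2.5), so dose would follow symptoms and glucose. More reductions under sham could hide a benefit, and more under taVNS could imitate one. If taVNS works, its arm may tolerate more metformin, which would dilute the symptom difference.

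**On current users.** Entry requires "Stable diet, exercise, lifestyle and antihyperglycaemic regimen", and the text does not say how the initial dose applies to someone already on metformin. A reader might count this as a further contradiction. It is operational detail that an article may leave to the full protocol, and it is not part of this point.

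**Conclusion.** The point holds in two parts of different weight.

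The threshold and the starting dose are inconsistent as written. The start of 1,000 mg/day is more than twice what a criterion-(2) participant can take, and the conflict persists for any threshold up to 1,000 mg/day. The documents do not settle which figure is wrong or how many participants are affected.

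The second part is an inexpensive improvement, not an error in the analysis. Dose reduction or a formulation switch in continuing users adds 0 to the dose-related items of the primary score and is in no listed efficacy or feasibility outcome. Differential dosing could mimic or mask a symptom difference, and neither its size nor its direction can be estimated from the documents. The absence of planned efficacy testing lowers the stakes, but the pilot's estimates still need dose by arm to be interpreted.

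This should be fixed; confidence is moderate, mainly because the 500 mg/day figure may be a misprint.

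**What to change.** **Threshold and start.** If 500 mg/day is an error, correct criterion (2) in 2.3.2, checking that the corrected value no longer conflicts with a 1,000 mg/day start. If it is intended, give criterion-(2) entrants a lower initial dose in 2.6.1, for example 500 mg once daily or less, with weekly escalation to the maximal tolerated dose. At 500 mg once daily the start is halved but equals the dose they are said not to reach, so only a lower start removes the conflict fully. State the trade-off: a lower start may reduce baseline or early symptom scores, leaving less room to show improvement over a 2-week treatment period.

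**Dose by arm.** In 2.7.3 and 2.10, add as descriptive outcomes by arm:

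- metformin dose (mg/day) at baseline, Week 2 and Week 4;
- the proportion with dose reduced, withheld or switched to extended release.

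Report these beside the primary score and the glycaemic results. Keep post-randomisation dose out of the mixed model: it responds to symptoms and possibly to treatment, so adjusting for it could distort the comparison.

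**Cost.** Protocol wording and one descriptive table. Dose adjustments are already recorded and entered in the case report form, so no new data collection is needed.
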